#### Caregiver psychological wellbeing

The 12-item General Health Questionnaire (GHQ-12; [44]) was developed to screen for non-specific psychiatric morbidity and has been widely validated and found to be reliable. It is commonly used as a screening tool to determine whether an individual is at risk of developing a psychiatric disorder. It comprises 12 Likert-type question items that measure a single dimension of psychological health. The Indonesian‐language version of the GHQ‐12 has been tested for reliability and validity, demonstrating good consistency and sensitivity (Idaiani & Suhardi, 2006).

#### Caregiver burden

The Involvement Evaluation Questionnaire (IEQ; [45] is a 31-item questionnaire comprising items relating to tension, supervision, worrying and urging and the degree to which the caregiver has experienced any of these. The scale has been developed for European settings, though it has been translated and validated in several European countries and in LMIC settings [46].

Carer burden will also be measured using the Experience of Caregiving Inventory which captures a wider set of negative subscales comprising difficult behaviours, negative symptoms, stigma, problems with services, effects on the family, loss and need for backup. There are two positive subscales consisting of positive personal outcomes and good aspects of the relationship with the patient about the carer’s experiences. This measure has been used with a variety of carers of mental health conditions, and each subscale has been reported to have satisfactory reliability [47].

#### Family functioning and environment

Expressed emotion (EE) will be measured using the Family Questionnaire (FQ; [48]). The questionnaire comprises 20 items each measured on a 4-point scale and consists of two subscales assessing both emotional over-involvement and critical comments. The FQ has excellent psychometric properties including a clear factor structure, good internal consistency of subscales and good inter-rater reliability in relation to the Camberwell Family Interview (CFI; [49]) which is the gold standard measure of EE and is sensitive to predicting components of EE.

#### Knowledge

Knowledge about schizophrenia and psychosis will be measured among participants using the Knowledge About Schizophrenia Test (KAST) [50] which was developed for caregivers of people admitted to hospital for treatment of psychosis. The test comprises 21 items regarding the aetiology, onset, symptomatology, outcome and treatment options. The measure shows excellent content validity and good criterion validity. This scale, the FQ, ECI and IEQ, will be cross-culturally adapted following similar procedures outlined by Knudsen et al. [51], comprising series of translations, back-translations and checking through qualitative inquiry with research assistants and participants in the feasibility study about item validity. Translation will be conducted by researchers independent of the study team, and back-translation will be conducted by the Indonesian researchers in the study team.

### Fidelity to the intervention model

Fidelity to the intervention will be measured using the Family Intervention in Psychosis Adherence Scale (FIPAS) [52]. The scale authors have demonstrated that the majority of items of the FIPAS have acceptable levels of inter-rater reliability. Healthcare workers delivering the intervention will keep a diary following each session to evaluate their opinions of fidelity, factors that they felt may have influenced their fidelity and their views regarding elements that were useful and those that were less useful. Treatment fidelity will also be monitored during qualitative inquiry with healthcare workers who have delivered the intervention. Pre-specified criterion for fidelity will be used interpreting 80–100% adherence as ‘high’ fidelity, 51–79% as ‘moderate’ and 0–50% as ‘low’ fidelity [53].

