### Outcomes and measures

The primary outcome is to determine the feasibility of family interventions delivered by non-specialist healthcare workers in primary care settings. Feasibility measures comprise evaluations of acceptability, recruitment, retention and fidelity to intervention components and delivery. Secondary outcomes relating to the feasibility of obtaining relevant measures for a full-scale trial comprise assessments of symptom severity and relapse rates, social functioning, family functioning and environment and therapeutic engagement. Analysis will comprise obtaining descriptive statistics and aggregating data to operationalise relapse as an outcome Table 2.

**Table 2 Tab2:** Variables, measures and assessment points

*Variable*	*Measure*	*Respondent*	*Eligibility*	*Baseline*	*Post-* *intervention*	*Three months post-intervention*	*Mode of administration*
Eligibility	Diagnosis		✅				Case note review
Participant age, gender, relationship to service user, service-user diagnosis, number of hours of contact per week, living status	Demographic measure	Family member	✅	✅			Self-report
Symptom severity	PANSS	Service user		✅	✅	✅	Researcher administered
Relapse rates	PANSS	Service user		✅	✅	✅	Researcher administered
Hospital episodes	Episode count	Service user		✅	✅	✅	Case note review
Social functioning	PSP	Service user		✅	✅	✅	Researcher-administered interview
Family environment and functioning	FQ	Family member		✅	✅	✅	Researcher-administered interview
Knowledge, attitudes, burden and general health	GHQ-28, ECI, KAST, IEQ	Family member, service user		✅	✅	✅	Researcher-administered interview
Therapeutic engagement	Attendance, retention in the intervention	Trial therapist			✅	✅	Researcher-administered interview
Fidelity to the intervention	FIPAS	Trial therapist			✅		Researcher-administered interview
Acceptability of the intervention	Therapist diaries of number of sessions attended	Trial therapist			✅		Self-reported therapist diaries
Satisfaction with the intervention	Qualitative interviews	Family member, service user and trial therapist			✅		Qualitative interviews and self-report questionnaires

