### Training and supervision

Healthcare workers will be trained in the intervention by an experienced, family intervention specialist, and we will train additional academic colleagues who will provide clinical supervision to healthcare workers in practice. The training will be delivered intensively over 1 week comprising 9 workshop sessions with skills practice and an additional session to establish a supervision framework and evaluate the delivery of training. Symptom evaluators will be trained to implement the interview schedule and assess symptoms by trained symptom evaluators among the study team. Symptom evaluators will be blind to treatment allocation, and inter-rater reliability will be measured on concordance between raters on a minimum of 5 standardised observer-rated symptom measures [39, 58]. As above, a supervision framework will be developed during training to ensure that healthcare workers in primary care settings have access to regular supervision with colleagues experienced in mental healthcare and education.

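### Fidelity rests on the therapists' own accounts, so the banded FIPAS score should be collected per session and reported as therapist-reported adherence

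*Protocol article*

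**What the plan says.** The protocol article, under Outcomes and measures, makes fidelity part of the primary feasibility outcome: "Feasibility measures comprise evaluations of acceptability, recruitment, retention and fidelity to intervention components and delivery".

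Under Fidelity to the intervention model it names the instrument, "Fidelity to the intervention will be measured using the Family Intervention in Psychosis Adherence Scale (FIPAS", and gives one measurement property for it: "The scale authors have demonstrated that the majority of items of the FIPAS have acceptable levels of inter-rater reliability". It then sets the grading: "Pre-specified criterion for fidelity will be used interpreting 80–100% adherence" as high, 51–79% as moderate and 0–50% as low.

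Table 2 gives the mode of collection. In the FIPAS row the respondent is the trial therapist, the only tick is at post-intervention, and the mode is "Researcher-administered interview".

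The fidelity section adds two further sources. One is a diary: "Healthcare workers delivering the intervention will keep a diary following each session to evaluate their opinions of fidelity". The other is qualitative inquiry with the workers who delivered the sessions.

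**The concern.** The reliability evidence and the data source do not match. Inter-rater reliability describes how closely different raters agree when they score the same material. It does not tell us whether that material is a true account of what happened in the sessions. Here the material is what the therapist recalls, after the course has ended, about their own work.

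The Background of the article makes delivery by non-specialist workers an aim of equal priority. The aims of the feasibility trial list fidelity separately, and the article says fidelity will inform intervention refinement and main-trial procedures. A high-fidelity label carried forward from therapists' own accounts could be read as evidence that task-shifted delivery works as intended. If delivery was in fact only moderate, the need for more training or supervision could be missed.

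**Working it through.** The document states no computed figure on fidelity, so there is nothing to reproduce. The check compares the sources and then uses simple arithmetic to show how much the interview has to summarise.

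**Who supplies the information, and when**

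| Source | Informant | Timing |
|---|---|---|
| FIPAS (Table 2) | Trial therapist, interviewed by a researcher | Once, post-intervention |
| Diary (fidelity section) | The worker who delivered the session | After each session |
| Qualitative inquiry (fidelity section; timing from the process evaluation section) | The workers who delivered the intervention | At intervention completion |

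All three sources have the same informant, the person whose adherence is being judged. The article states no observation or recording of sessions, which are home visits. The inter-rater check described under Training and supervision concerns symptom measures, not the FIPAS.

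**How much one interview has to cover**

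Inputs from the Methods: 30 dyads in the intervention arm, up to 10 sessions per family, 12–15 healthcare workers.

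- Sessions in total: 30 × 10 = up to 300.
- If there is one FIPAS per worker: 12 to 15 scores. With families spread evenly, each worker has 30/15 = 2 to 30/12 = 2.5 families on average, so a score summarises up to 20 to 25 sessions.
- If there is one FIPAS per dyad: 30 scores, each summarising up to 10 sessions.

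The article does not say which unit applies. Under either one, the score looks back over a whole course of sessions.

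**What over-reporting would do at the 80% boundary**

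The amount of over-reporting is an assumption, because the document gives no figure. True adherence of at least (80 − over-report) would be labelled high.

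| Assumed over-report (percentage points) | True adherence moved from moderate to high |
|---|---|
| 0 | none |
| 5 | 75–79% |
| 10 | 70–79% |
| 15 | 65–79% |

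This shows which scores would be exposed. It does not estimate how many therapists or families would be affected.

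**The case against.** **A researcher may do the scoring.** A reader might infer that the FIPAS is purely self-rated. Table 2 does not say so. It lists a researcher-administered interview and describes the diaries separately as self-reported. The PSP has the service user as respondent and the same mode, yet its own section calls it observer-rated. On that pattern a researcher may assign the FIPAS scores, and inter-rater reliability then has some relevance. This stands, but the information still comes from the therapist, and agreement between scorers cannot correct a shared, inaccurate account.

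**Fidelity does not rest on one score.** The diary is kept after every session and the qualitative work adds context. This also stands. Neither source is independent of the therapist, however, and the article does not place the FIPAS items in the diary.

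**The article is condensed.** The full protocol may describe independent session ratings. The point does not depend on that omission. It depends on the mode of collection that Table 2 states.

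**Stronger readings that the document does not support:**

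- That the result *will* be optimistic, or by a known amount. The direction is the expected one, but with no over-reporting nothing is mislabelled.
- That a progression decision turns on the 80% cut-off. The three success criteria concern dyad recruitment, healthcare worker recruitment and completion of outcome measures. Fidelity is not among them.
- That the bands leave scores unclassified between 50 and 51% or between 79 and 80%. They read as whole-percent bands, and rounding closes the gaps.
- That the planned supervisors could easily provide independent ratings. The article says "we will train additional academic colleagues who will provide clinical supervision to healthcare workers in practice", but it does not describe them attending or hearing recordings of the home visits. Scores given in supervision would again rest on the worker's account, and independent scoring would need resources that are not planned.

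**Conclusion.** The point holds in a limited form. Every stated fidelity source depends on the therapist, and the main one is a single retrospective interview. The published inter-rater reliability does not establish that such an account is accurate. Labelling the resulting score as high fidelity from 80% is therefore likely to overstate delivery quality.

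The size cannot be estimated from the document. The direction rests on the assumption that people describing their own adherence after the event tend to over-report rather than under-report it. The consequence falls on the feasibility conclusion about task-shifted delivery and on refinement of the intervention, not on a formal go/no-go rule. The change is worth making because it is cheap and alters what the trial can fairly conclude, but the flaw does not put the trial's design in question.

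**What to change.** 1. **Collect adherence per session.** Add the FIPAS items to the diary that workers already complete after each session, and keep the end interview as a supplement. This shortens the recall period. It does not make the information independent, so the second change is also needed.
2. **Change the label in the fidelity section.** Report the banded result as *therapist-reported adherence*. State that no high-fidelity conclusion about task-shifted delivery will be drawn from it unless sessions are independently rated.

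The cost is a slightly longer diary form and a more cautious fidelity statement. No new staff, visits or recordings are required.

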### Qualitative process evaluation

Qualitative interview data on participants’ views of the intervention will be obtained in individual, semi-structured interviews at intervention completion. These interviews will be digitally recorded, transcribed, checked for accuracy and analysed using framework analysis [54]. Again, data will be analysed by Indonesian researchers, and a sample of scripts (20%) were transcribed, translated and coding frame agreed with the wider study team at UI and UoM. Process evaluation will be informed by the Medical Research Council guidance on process evaluation in designing and testing interventions [55]. We will use a version of the Consolidated Framework for Implementation Research optimised for use in low- and middle-income countries [56] to conduct an implementation analysis that will also inform the feasibility trial which will be finalised prior to a definitive trial utilising qualitative data regarding trial processes integrated with qualitative data collected during the intervention development.

### Procedures

Data will be collected from participants in intervention and control groups at three time points: pre-intervention, post-intervention and 3 months later. Participants within the control group will receive treatment as usual. Standard care comprises limited community services in primary care settings providing public education, counselling, basic psychiatric services [57] and the provision of pharmacological treatment and monitoring at out-patient facilities at regional mental health hospitals. As an active comparator and to evaluate the amount of treatment received by both arms of the trial, all participants will be asked about the extent of treatment and intervention received at regional hospitals and local primary care centres. Demographic data collected include age, gender, ethnicity, marital status, education, and employment will also be collated. As appropriate, we will gather information about the living arrangements, primary diagnosis of service user, duration of the caring role, number of people cared for, relationship to the person with schizophrenia, whether they live with the person, level and type of contact and whether they are receiving support from mental health services. Healthcare professionals will provide information about the nature of their work and whether they have received specific mental health training, contact with people with mental health problems and duration of service Table 3.

**Table 3 Tab3:**
[figure not shown]
Study enrollment and interventions

### Procedure for randomisation and blinding

Online randomisation services will be provided by a telephone randomisation service (www.sealedenvelope.com), and participants will be allocated in a 1:1 ratio. Randomisation will be conducted according to the International Conference on Harmonization E9 Statistical Principles Guidelines and will be implemented by the trial manager. Upon confirmation of eligibility by the principal investigator in Indonesia (HS), the participant will be randomised to one of the treatment arms. Allocation sequence will be kept from the study researchers responsible for obtaining baseline, and outcome measures and trial management personnel responsible for allocation will work in separate locations. Participants will be asked not to reveal their allocation to the study researchers/study evaluators.

### Training and supervision

Healthcare workers will be trained in the intervention by an experienced, family intervention specialist, and we will train additional academic colleagues who will provide clinical supervision to healthcare workers in practice. The training will be delivered intensively over 1 week comprising 9 workshop sessions with skills practice and an additional session to establish a supervision framework and evaluate the delivery of training. Symptom evaluators will be trained to implement the interview schedule and assess symptoms by trained symptom evaluators among the study team. Symptom evaluators will be blind to treatment allocation, and inter-rater reliability will be measured on concordance between raters on a minimum of 5 standardised observer-rated symptom measures [39, 58]. As above, a supervision framework will be developed during training to ensure that healthcare workers in primary care settings have access to regular supervision with colleagues experienced in mental healthcare and education.

### Research data management

The project will primarily use the Research Data Service at UI to store, manage and curate data. Data will be stored using Word and Excel documents and transferred to research analysis software when required for analysis and distribution checks. Quality checks will be conducted periodically, and coding will be overseen by the study teams at UI and UoM. We will also utilise the UoM Research Data Management Service (RDMS) which provides, managed and secure replicated storage. The RDMS allows researchers to securely transfer digital data to UoM and can be used to store, manage and curate data to preserve this after the lifecycle of the project. Non-digital data, e.g. consent forms and manuals generated from the research programme, will be stored in stand-alone locked cabinets held in a secure location in UI. Data will be stored in raw, processed, analysed and final dataset format to ensure quality and will be transferred between host and sponsor university using Dropbox for Business.

### Trial oversight

The study is supported by a Research Advisory Group (RAG) who are independent of the study team and comprises service users, carers and advocates, healthcare professionals and primary care workers, academics, community leaders and government healthcare officials (*n* = 11). The RAG provide insight and information on the needs of the researchers and the research project using pre-specified terms of reference. The group has provided expertise on research processes and intervention development including comment on analysis of qualitative data, comment on the presentation of intervention and training manuals once developed and comment on assessment schedules for the feasibility study. Additionally, the RAG will provide oversight to the feasibility trial as a Trial Steering Committee chaired by a separate member than oversight of the RAG. The steering committee will approve the final protocol before the feasibility trial commences. The RAG will also take a lead role in the dissemination phase devising plans for investigators and sponsor to communicate trial results to participants, healthcare professionals, the public and other relevant groups. The group will be chaired by the Director of Mental Health and Drug Control, Ministry of Health in Indonesia. Additional service-user and carer representatives will be recruited at each phase and service-user involvement organised by our charity partners Komunitas Peduli Skizofrenia Indonesia (KPSI). KPSI is a user-led charity which runs peer support groups, education and anti-stigma activities in health services and local communities.

## Discussion

This study will provide important information on the feasibility of delivering family interventions for people with schizophrenia who reside in circumscribed areas of Indonesia. The intervention has a solid evidence base for delivery in high-income settings and is a NICE recommended intervention and the model of choice in NHS trusts [26, 59]. Importantly, family interventions have been successfully adapted to minority populations in the UK [60] and in other low-resource settings [61, 62]. As far as we are currently aware, these types of interventions have not previously been adapted culturally to Indonesian populations and contexts nor have co-production methods been utilised in this way to develop an intervention informed by stakeholder perspectives, preferences and priorities, and the findings of this trial will provide a unique and novel contribution to knowledge of family interventions for schizophrenia in this context.

We have focused on implementation within the development phase of this research to ensure that family interventions can be embedded within existing healthcare delivery settings using the more extensive network of primary care services available in Indonesia. Mental health treatment is often provided by mental health professionals whose names and qualifications are maintained in a central government register, and they are licensed to practice in specialty settings. These specialist mental health providers are not readily available in Indonesia due to manpower and resource shortages, fledgling professional development, economically challenged populations and a lack of mental health as a priority in policy agendas. As an example, mental health nurses in Indonesia are not regulated by government legislation, and degree courses have only been available since 2005 [63], and our approach is a unique strength of this study.

Guided by the World Health Organizations promotion of task-shifting models, our aim is to increase capacity for intervention delivery recognising the need for integration between primary and secondary mental health services and to develop family interventions that can be delivered by non-specialist professionals and are scalable [64]. While this is a novel approach in Indonesia, recruitment to our feasibility trial may be challenged by having fewer staff resources to deliver family interventions particularly as we have chosen an individualised intervention. Nonetheless, family interventions delivered intensively have a strong evidence base [10], and our choice partly reflected service-user and carers stated preference for personalised, tailored interventions. Utilising patient-centred approaches and co-design to develop intervention content and processes may also help to overcome challenges of recruiting dyads, which has previously been problematic in family intervention research and practice [17, 65]. To date, we have successfully recruited participants for the first two phases of the project, collected qualitative data and analysed and synthesised findings to inform our culturally adapted manual of evidence-based family interventions. Our coadapted and refined intervention will be administered in this feasibility trial informed by stakeholder preferences and priorities. Our approach aims to enhance the acceptability of and satisfaction with the intervention through embedding relevant and culturally sensitive content and processes within the intervention training and delivery.

Conducting a feasibility study presents multiple opportunities to refine procedures and processes to inform conduct of a more definitive trial at a later point. Indeed, the aim of this trial is to inform the further development of both the intervention and a larger trial with sufficient power to determine the cost and clinical effectiveness of family interventions. We aim to optimise the intervention and trial processes using the oversight of the Trial Steering Committee in determining the feasibility and acceptability of the intervention for a future trial. Our anticipated findings will be a refined, testable, manualised intervention that aims to reduce relapse for people with psychosis and schizophrenia. We will be able to determine whether we can feasibly recruit sufficient participants to test the effects of the intervention and recruit sufficient healthcare workers to determine whether they can be adequately trained to provide such an intervention in its intended format.

